### Trial design {8}

The study is a monocentric, prospective, confirmatory randomized controlled trial with three experimental conditions: (1) START NOW as web-based group training guided by a facilitator, (2) START NOW as web-based pure self-help training, and (3) TAU. Institutions are randomly assigned 2 weeks before the 9-week intervention phase.

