## Methods: participants, interventions, and outcomes

### Study setting {9}

The study is conducted by the Department of Child and Adolescent Psychiatry, University Psychiatric Clinics Basel. Data is collected in RYC a CI recognized by the Federal Office of Justice (FOJ) [39] throughout the German and French-speaking parts of Switzerland. Assessments are conducted at five time-points (T). First to screen for eligibility (T_0_), then before intervention start (T_1_), immediately following intervention end (T_2_), 12 weeks ± 2 weeks after intervention end (T_3_), and 24 weeks ± 2 weeks after intervention end (T_4_).

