### Eligibility criteria {10}

Inclusion criteria are listed in Table 1.

**Table 1 Tab1:** Eligibility criteria for institutions and participants

Inclusion criteria for institutions:	Inclusion criteria for participants:
• Institutional consent • Ability to offer a 9-week group training guided by a facilitator • At least two designated START NOW trainers that successfully complete the full 1.5 days of training • Internet access for participants • Guarantee of standardized implementation	• AYA in RYC or CI • Ages 14 to 24 years • Sufficient German or French language skills • Participant consent • AFQ-Y sum score ≥ 34.05 • MAYSI-2 subscale angry-irritable sum score ≥ 5.0 • MAYSI-2 subscale depressed-anxious sum score ≥ 3.0 • No concurrent group-based skills training

*Note. AYA* adolescents and young adults*; AFQ-Y* Avoidance and Fusion Questionnaire for Youth; *MAYSI-2* Massachusetts Youth Screening Instrument-2. Participants with high scores on MAYSI-2 subscales Suicide-Ideation (≥ 2) or Thought-Disturbance (≥ 2) are individually assessed with caretakers. Suicidal or otherwise acutely endangered participants are excluded

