### Outcomes {12}

#### Primary endpoints

The primary focus is on the post-intervention psychological inflexibility measured by AFQ-Y scores between baseline (T_1_) and follow-up (T_3_) (12 weeks +/− 2 weeks after end of intervention). The AFQ-Y is a validated self-rating questionnaire assessing PF in adolescents and young adults. Items are based on ACT models of human suffering representing the theoretical concept of psychological inflexibility due to high cognitive fusion and experiential avoidance [37]. Participants answer 17 items indicating how true each item is for them on a 5-point Likert scale (0 = not at all true; 4 = very true). Higher total scores indicate lower PF. Data will be assessed within 2 weeks before start of skills training (baseline, T_1_), within 2 weeks after end of skills training (T_2_), as well as at 12 weeks (+/− 2 weeks) (T_3_) and 24 weeks (+/− 2 weeks) (T_4_) post skills training. Primary endpoint is the change in total score between baseline (T_1_) and follow-up (T_3_). Total scores can range between 0 and 68. Accordingly, a change in score can range between − 68 and + 68.

Further objectives of the current trial are to assess the effect of treatment (immediately after the end of intervention) on other psychological health-related outcome measures (i.e., general resilience, psychological well-being, self-efficacy, general impairment, anger-irritability, training substance use) in participants of the three conditions. Furthermore, resilience will also be assessed for caretakers.

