**Fig. 1 Fig1:**
[figure not shown]
Trial schedule *Note. T*_*1*_,* T*_*2*_,* T*_*3*_,* T*_*4*_ time points; *AFQ-Y* Avoidance and Fusion Questionnaire for Youth; *MAYSI-2* Massachusetts Youth Screening Instrument-2; *CD-RISC* Connor-Davidson Resilience Scale; *WHO-5* World Health Organization – Five Well-Being Index; *CIS* Columbia Impairment Scale; *PHQ-4* Patient Health Questionnaire-4; *SWE* Skala zur Allgemeinen Selbstwirksamkeitserwartung [General Self-Efficacy Expectancy Scale]; *CSQ* Client Satisfaction Questionnaire; *ARI* Affective Reactivity Index; *EssenCES* Essen Climate Evaluation Schema; *TSQ* Trainer Satisfaction Questionnaire*.* Data will be collected at screening (T_0_), ≤ 4 (+ 2) weeks before the intervention (T_1_; baseline assessment), ≤ 2 weeks after the intervention has ended (T_2_; post-intervention assessment), 12 ± 2 weeks post intervention (T_3_; first follow-up), and 24 ± 2 weeks post intervention (T_4_; second follow-up)

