### Sample size {14}

The sample size estimation was performed in statistical software R using a simulation-based approach. The sample size estimation is based on the assumptions, that standard deviations of AFQ-Y scores are equal for all groups and conditions, and that the mean baseline scores of all groups are equal due to randomization. We assumed the AFQ-Y scores at baseline to be normally distributed with a mean of 21.04 and standard deviation of 13.01 [37]. Further, we assumed a high correlation of AFQ-Y scores within participants between time-points, with a Pearson correlation coefficient of *r* ~ = ~ 0.80. The effect sizes of the intervention in standardized Cohen’s *d scores were* = -.50 for TAU vs. web-based self-help training and Cohen's *d* = -.80 for TAU vs. web-based group training.

The above assumptions regarding distribution, correlations, and effect sizes were used to determine the required sample size with a simulation-based approach. Based on the above assumptions and distributions, 9999 synthetic data sets of different sample sizes were generated. The primary analysis was applied to each of these data sets. The simulations showed that at an effective sample of *N* = 78 (26 participants per condition) would enable us to reject the null hypothesis with the desired power of 80%.

In the next step, we corrected this sample size for the design effect (i.e., clustering of participants in groups), assuming a weak resemblance in the AFQ-Y score of patients within the same group (rho = 0.2) [53]. Before the start of the study, we assumed a group size (i.e., participants receiving the intervention together) of on average 9 participants. During a sample size re-estimation, this number was reduced to 4 participants per group as was observed in the study centers. With an estimated drop-out rate of 20% [17], 150 patients (i.e., 50 patients per condition) must be recruited to reject our null hypothesis at a power of 80% considering the effect of clustering. The expected flow of participants from recruitment through the end of the study is shown in Fig. 2.

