### Assignment of interventions: allocation {16}

#### Sequence generation {16a}

The randomization process will occur at the institutional level when a minimum of four eligible participants were available (gave informed consent and passed screening). Participants will be randomized within fully eligible groups of 4 to 12 individuals, stratified by study site and across 3 conditions. Institutions will be randomized using a pre-generated list, generated using the statistical software R, inaccessible to the research team, and provided and implemented through the DCR at the University of Basel.

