### Statistical methods {20}

#### Statistical methods for primary and secondary outcomes {20a}

A detailed statistical analysis plan will be written by the study statistician and kept under version control at the DCR. The statistical analysis plan will be finalized before the last visit of the last patient and the final version will be stored before access to the study database is granted.

All outcomes of interest will be described stratified by intervention group at each of the time-points of assessment by mean and standard deviation, median, or median and interquartile range, as appropriate. We will also visualize the time course of the endpoints of interest by intervention group.

The primary objective is to compare the follow-up AFQ-Y score (12 ± weeks after the end of the intervention) between the 3 intervention arms. To this end, we will perform an intention-to-treat analysis, analyzing all participants in the groups they were randomized to, regardless if they actually completed the particular intervention. We will use the imputed full analysis set for the primary analysis. The primary endpoint is the change in AFQ-Y score from baseline (T_1_) to the first post intervention follow-up (T_3_, 12 ± weeks). We will fit a linear mixed-effects model for the primary endpoint post intervention AFQ-Y score. The identifier of the institution group will be included as a random intercept to account for the clustered data structure (i.e., participants in training groups within institutions). The intervention (3 levels with TAU as reference) will be included as a fixed effect of interest, and the baseline AFQ-Y score is included in the model as a covariate. We will examine the distribution of the residuals to assess the model assumptions. The estimate of the fixed effect will be presented together with the corresponding 95% confidence interval and p-value. All analyses will be performed in R version 4.3.1 or higher.

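### The screening AFQ-Y score (T0) is left out of the primary model; adding it as a second covariate would be an almost free, modest gain in precision to a model that is already valid

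*Protocol article*

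**What the plan says.** Two AFQ-Y scores precede the intervention. Under Study setting {9} screening and baseline are separate assessments: "First to screen for eligibility (T_0_), then before intervention start (T_1". Table 1 under Eligibility criteria {10} requires "AFQ-Y sum score ≥ 34.05", so AFQ-Y must be scored at screening. Under Sequence generation {16a} an institution is randomised once at least four participants have met the condition "gave informed consent and passed screening". T0 therefore precedes allocation.

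The primary endpoint is the change from T1 to T3. Under Statistical methods {20a} the primary model is a linear mixed model for the follow-up AFQ-Y score with intervention as a three-level fixed effect, a random intercept for the institution group, and one further covariate: "the baseline AFQ-Y score is included in the model as a covariate". Baseline is defined there as T1. T0 AFQ-Y has no stated role in this model.

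Under Sample size {14}, "we assumed a high correlation of AFQ-Y scores within participants between time-points, with a Pearson correlation coefficient of" about 0.80. One value is given, and T0 is not named.

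**The concern.** An earlier score on the outcome scale is usually among the best predictors of a later one. If single AFQ-Y scores carry occasion-specific noise, T0 and T1 together describe a participant's usual level better than T1 alone. Leaving T0 out then makes the residual variance, and so the standard error of both primary contrasts, larger than the collected data require.

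The contrast with something to gain is self-help versus TAU, which has the smaller assumed effect. The article anticipates high dropout and reports that recruitment has ended, so lost precision cannot be bought back by enrolling more participants.

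The timing of T1 adds a smaller reason to give T0 a role. Trial design {8} says "Institutions are randomly assigned 2 weeks before the 9-week intervention phase". The Primary endpoints section says "Data will be assessed within 2 weeks before start of skills training (baseline, T_1", while the note to Fig. 1 gives "≤ 4 (+ 2) weeks before the intervention (T_1_; baseline assessment". On the first of these windows T1 may fall after allocation, which is not blinded. T0 is the score that is certainly collected before it.

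**Working it through.** **Inputs.** From Sample size {14}: mean 21.04, SD 13.01, r = 0.80, d = -0.50 (self-help versus TAU) and -0.80 (group training versus TAU), 26 effective participants per condition, ICC 0.2, group size 4, 20% dropout, 50 recruited per condition. From Table 1: cut-off 34.05. Assumed: two-sided alpha 0.05 (not stated; the hypotheses are two-sided and 95% intervals are planned), normality, and every correlation that involves T0.

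**Formula.** Power = Φ(d / √(2v/n) − 1.96), where v is the residual variance in units of the total variance and n is the effective number per arm.

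**1. Reproduce the plan's figure (d = 0.50).**
- Change score: v = 2(1 − 0.80) = 0.40. At n = 26, power is 81.3% (80.3% with a t reference; 80.0% in a 9,999-run simulation). The stated 26 per condition and 80% reproduce.
- Adjustment for T1, as in the stated model: v = 1 − 0.80² = 0.36. At n = 26, power is 85.2% (84.3% with t; 83.3% in simulation).
- Recruited sample: the design effect is 1 + (4 − 1)(0.2) = 1.6, and 78 × 1.6 × 1.2 = 149.8, which matches the stated 150.
- After dropout and clustering: 50 × 0.8 / 1.6 = 25 effective per arm. T1-only power is then 83.8%. This n is used below.

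**2. Add T0, all three correlations 0.80, no entry selection.** v = 1 − 2(0.80²)/(1 + 0.80) = 0.289. Power is 90.8%, a gain of 7.0 points (6.6 at n = 26).

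**3. Apply the cut-off at T0.** (34.05 − 21.04)/13.01 = 1.00, so entry starts one SD above the assumed mean.
- Truncation leaves Var(T0) = 0.199.
- Var(T1) = Var(T3) = 1 − 0.64(1 − 0.199) = 0.487, and Cov(T1,T3) = 0.80 − 0.64(1 − 0.199) = 0.287.
- Given T1 alone, v = 0.487 − 0.287²/0.487 = 0.318. Given T0 and T1, v stays at 0.289.
- Power is 88.0% against 90.8%, a gain of 2.8 points (2.6 at n = 26). With d defined on the narrower SD of the enrolled sample, the gain is 4.1 points, from a lower starting power.

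**4. Let the T0-T3 correlation fall, with T0-T1 and T1-T3 held at 0.80.**

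| T0-T3 correlation | v with T0 and T1 | Gain, no selection | Gain, cut-off at T0 |
|---|---|---|---|
| 0.80 | 0.289 | 7.0 | 2.8 |
| 0.72 | 0.342 | 1.8 | 0.7 |
| 0.64 (= 0.80 × 0.80) | 0.360 | 0 | 0 |

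If instead T0 correlates 0.7, 0.6 or 0.5 with both later scores, without selection, the gain is 3.8, 2.3 or 1.3 points.

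**5. Group training versus TAU (d = 0.80).** Without selection and with all correlations 0.80, power goes from 99.7% to 99.95%, about 0.2 points. With the cut-off it goes from 99.89% to 99.95%.

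**The case against.** The strongest reply is that nothing here is wrong. A mixed model of T3 AFQ-Y on arm and T1 AFQ-Y, with a random intercept for the group, is standard and agrees with the endpoint definition. On the closed-form calculation it already exceeds the power target. That stands, and it is why this is an improvement and not a correction.

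A reader might infer that the plan loses about 7 points of power on its own inputs. The documents do not support that. The figure needs r = 0.80 extended to T0, which the sample size section never mentions, and it needs the plan's own cut-off to be ignored. The equality of the correlations is what produces the gain. Decay is plausible, because T0 has no stated window and T3 comes after nine weeks of training plus twelve weeks.

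The closed form also holds the design effect at 1.6, as if T0 explained between-group variance in the same proportion as individual variance. If the group component is untouched, the gain falls to 4.4 points without selection (83.8% to 88.2%) and 1.8 with it (88.0% to 89.8%).

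A reader might also infer that the T1-only model leaves the trial short of 80%. With a t reference on 18 degrees of freedom (two arms of ten groups of four completers) power is about 79.6%. On 27 degrees of freedom (all three arms) it is about 81%. The reserve is thin on that view, but the power target is not endangered by the choice of covariate.

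Finally, T0 is not necessarily discarded altogether. The imputation model draws on relevant baseline values, which could include it, and a detailed SAP is still to come. But the article does state the covariates of its confirmatory model, and T0 is not among them.

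**Conclusion.** The point holds as a modest, nearly free gain in precision. AFQ-Y is available at T0 before randomisation, and the stated primary model does not use it. For self-help versus TAU the gain in power is 0 to about 7 points: about 3 with equal correlations of 0.80 and the cut-off at T0, and none if the T0-T3 correlation is 0.64. For group training versus TAU it is about 0.2 points or less.

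The range rests on assumed T0 correlations, two-sided alpha 0.05, normality, and the cut-off applying to every participant. Table 1 does not say whether its score criteria are joint or alternative. If they are alternative, selection is weaker and, with equal correlations, the gain lies between about 3 and 7 points. The T1-only model is valid, so this is an optional recommendation of low severity.

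**What to change.** In the SAP, add the T0 screening AFQ-Y as a second fixed covariate beside T1 in the primary model: T3 AFQ-Y on arm, T1 AFQ-Y and T0 AFQ-Y, with the random intercept for the institution group. Do the same in the T2 and T4 AFQ-Y models, and fix it before database access. T0 is measured before allocation, so neither adjusting for it nor selecting on it biases the treatment contrast. Adding T0 would not by itself repair a T1 score answered after allocation was known, so the stated T1 windows should be reconciled with the time of randomisation separately.

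The cost is one line of text and one degree of freedom, with no new data.

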#### Interim analyses {21b}

No interim analysis was planned for this study. Given the low risk of the intervention, we did not expect any safety concerns that should be evaluated by an independent data safety and monitoring committee. Furthermore, we did not consider an adaptive trial design and re-evaluation of the sample size during the trial, or stopping due to futility, due to the short duration of recruitment and time between recruitment and primary endpoint assessment.

#### Methods for additional analyses (e.g., subgroup analyses) {20b}

As a secondary objective, we aim to assess the intervention effect in the subset of compliers (i.e., per protocol analysis). We define a participant as a complier if this participant completed at least 50% of the planned group-based training sessions, or if this participant completed at least 50% of the web-based self-help program. The endpoint is the same as for the primary analysis, and the same analysis will be performed on this subset of the full analysis set.

Furthermore, we plan to perform a sensitivity analysis to assess the effect of the imputations on the outcome of the primary analysis. To this end, we will perform the primary analysis on the available-case data set, including all patients without missing data for the variables used in the primary analysis.

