##### Adherence

For each institution, the quality of the group training guided by a facilitator will be rated by a START NOW facilitator during the second session (either live or via online connection) using a *Quality Assurance Form* [40]. Furthermore, participant adherence will be recorded through a) attendance lists created by caregivers in the group condition and b) usage logs of the WebApp, specifically finished sessions.

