##### Handling missing data

We will use multiple imputation to address the issue of missing outcome values for both primary and secondary endpoints. Missing values will be imputed using Multivariate Imputation by Chained Equations with relevant baseline values and if available values at other follow-up time-points of the focal endpoint.

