### Limitations

The trial has several limitations. First, challenges to engage institutions and participants arise from limited resources and the lack of motivation to participate in a study. Secondly, we anticipate a high dropout rate due to AYA who are difficult to reach. The lengthy 9-month duration of the trial, influenced by factors such as holidays and relocations, contributes to this expectation. Thirdly, recruitment difficulties also stem from structural variations among institutions, non-participation due to resource constraints on the institutional side, and scheduling challenges during vacations. Additionally, the extended follow-up periods post intervention constitute a fourth challenge that may impact participant engagement. Lastly, self-help interventions and questionnaire adherence exhibit low levels among participants, contributing to the overall limitations. These challenges underscore the necessity for cautious result interpretation.

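### The one check named for the imputation, an available-case analysis, rests on a stricter form of the same missing-at-random assumption, so agreement would not show robustness

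*Protocol article*

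**What the plan says.** All references are to the protocol article.

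- **Target and data set ({20a}).** The primary analysis is intention to treat, "analyzing all participants in the groups they were randomized to, regardless if they actually completed the particular intervention". On the data: "We will use the imputed full analysis set for the primary analysis".
- **Imputation (Handling missing data, under {20c}).** The method is "Multivariate Imputation by Chained Equations with relevant baseline values and if available values at other follow-up time-points of the focal endpoint". Session completion is not named as a predictor.
- **Check on the imputation ({20b}).** The purpose is given as "we plan to perform a sensitivity analysis to assess the effect of the imputations on the outcome of the primary analysis". The content is "we will perform the primary analysis on the available-case data set, including all patients without missing data". No other sensitivity analysis for missing outcomes is named.
- **Adherence data (Adherence, under Outcomes {12}).** Attendance lists are kept in the group condition, together with "usage logs of the WebApp, specifically finished sessions". In the stated analyses these data serve only to define compliers (at least 50% completed) for the per-protocol set.
- **Expected losses.** Sample size {14} plans for 20% drop-out. Limitations expects high dropout among young people who are hard to reach, and adds that "self-help interventions and questionnaire adherence exhibit low levels among participants".

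**The concern.** An intention-to-treat effect includes participants who abandon the training. If such a participant also stops answering, the T3 score has to come from the imputation model. That model knows the participant's baseline and whatever other AFQ-Y scores exist, but not that the training was abandoned. If abandoning it goes with a smaller benefit, the imputed score is too favourable to the active arm.

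A sensitivity analysis should help the reader judge how much this matters. Available-case analysis cannot: it leaves the same participants out and estimates the effect from those who answered, with less information than the imputation uses. If the two results agreed, a reader could take that as robustness to missing data when the assumption they share had not been tested. This is a confirmatory trial that itself expects substantial loss, so the point bears on the main result.

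**Working it through.** **1. The plan's figures.** Sample size {14} gives a baseline SD of 13.01, a within-person correlation of 0.80, rho = 0.2, groups of 4, effects of −0.50 (self-help) and −0.80 (group) against TAU, and 20% drop-out. In points the effects are 0.50 × 13.01 = 6.5 and 0.80 × 13.01 = 10.4. The recruitment total reproduces: 78 × (1 + 3 × 0.2) = 124.8, and 124.8 × 1.20 = 149.8, so 150. I take 20% as the share missing at T3. The article gives no figure for bias from missing data.

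**2. The two assumptions side by side.**
- Available-case, adjusted for baseline: given arm and baseline, missing and observed T3 scores have the same mean.
- Multiple imputation: the same, given arm, baseline and any observed T2 or T4 score. Arm is taken to be in the model; the article does not name it.

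If T2 and T4 are also missing, the two conditions are the same. If T2 is present, imputation assumes less. In neither case does available-case relax what imputation assumes.

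**3. Closed form for available-case.** Assume non-adherers gain nothing and TAU missingness is uninformative. Let m be the overall share missing in the active arm and m_a the share missing among adherers. Then

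observed effect / ITT effect = (1 − m_a) / (1 − m).

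With m = 0.20:
- m_a = 0.10 gives 0.90/0.80 = 1.125
- m_a = 0.05 gives 0.95/0.80 = 1.19
- m_a = 0 gives 1/0.80 = 1.25

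**4. Simulation.** One active arm was compared with TAU, with correlation 0.80, ICC 0.2, groups of 4, 20% missing at T3, and the ITT effect held at the plan's value. The non-adherence and missingness rates are assumptions. T4 was not simulated. Ratios to the full-data effect for self-help (true effect about −6.5 points):

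| Non-adherent | Missing: non-adherers / adherers | Available-case | MI, T2 observed | MI, T2 also lost |
|---|---|---|---|---|
| 40% | 35% / 10% | 1.12–1.13 | 1.06 | 1.12 |
| 40% | 42.5% / 5% | 1.19 | 1.08 | 1.19 |
| 30% | 43.3% / 10% | 1.12–1.14 | 1.06 | 1.14 |
| 50% | 40% / 0% | 1.26 | 1.10 | 1.26 |

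For the group arm (−0.80) the ranges were 1.12–1.25, 1.04–1.07 and 1.11–1.25.

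At about trial size (48 per arm, first row, T2 lost for half of those missing T3), the means were −6.4 (full data), −6.9 (MI) and −7.2 (available-case). Available-case was at least as large as MI in 69% of simulated trials. It therefore tends to make an overstated imputed result look confirmed or even cautious.

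**5. Adding session completion to the imputation.** In these scenarios the ratio returned to 0.99–1.01. In a separate run, with 52 per arm and almost all missing participants non-adherent and lost from T2, the full-data effects were −0.393/−0.639 (self-help/group), MI gave −0.483/−0.786, and MI with session completion gave −0.461/−0.752. Since 0.461/0.393 = 1.17 and 0.752/0.639 = 1.18, most of the bias remains, because too few non-adherers are observed to learn from.

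**6. Direction.** Let δ be the amount by which true missing scores exceed (are worse than) the modelled ones. Then

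true difference = estimated difference + m_A·δ_A − m_T·δ_T,

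where A is the active arm and T is TAU. With m_A = 0.20, δ_A = 6.5 and δ_T = 0, the estimate moves by 1.3 points towards zero; for the group arm the shift is 0.20 × 10.4 = 2.1. If instead m_T = 0.20, δ_T = 6.5 and δ_A = 0, the planned analysis understates the effect by 1.3 points.

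**The case against.** **The analysis plan may cover it.** {20a} promises a detailed statistical analysis plan, the list of imputation predictors is not said to be exhaustive, and {20b} does not say that available-case is the only sensitivity analysis. That is fair, and further analyses may exist. But the article goes beyond leaving the matter open: it names the predictors, the check and the purpose of the check, and the check named cannot test the assumption.

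**Comparing results with and without imputation does show the effect of imputing.** Literally true, and the article does not claim to test missing at random. What stands is that agreement should not be read as robustness.

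**A reader might infer that the protocol predicts non-adherers will be the ones who go missing.** It does not. Limitations links dropout to young people who are hard to reach, holidays and relocations, and mentions low self-help and questionnaire adherence separately. It does not say these are the same people, and it says nothing about low adherence in the facilitated group. Vouchers are paid for questionnaires, which partly separates answering from training.

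**A reader might also infer a bias of 20–25% with both analyses giving the same answer.** That holds only when nearly all the missing participants are non-adherers without benefit and all their later scores are lost. A participant's own T2 or T4 score enters the imputation when available; with T2 observed, the MI bias falls to about 4–10% and the two analyses separate. The non-adherence, benefit and missingness rates are assumptions, not figures from the plan.

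**Conclusion.** The point holds in a conditional form. The named check uses a stricter missing-at-random assumption than the analysis it is meant to examine, so it cannot reveal a departure from that assumption. This is so whatever the true rates are.

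The size is conditional. It assumes 20% missing, 30–50% of active-arm participants non-adherent with no benefit, T3 missing in 35–43% of them against 0–10% of adherers, and uninformative loss in TAU. Overstatement is then about 4–10% for multiple imputation when T2 is observed, 11–25% when all later scores are lost, and 12–26% for available-case. The documents make such a pattern plausible but do not establish it, and worse outcomes among TAU dropouts could offset or reverse it. The intention-to-treat analysis with multiple imputation is conventional and not contradictory. The weakness lies in the check and in leaving recorded adherence out of the imputation.

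Whether arm enters the imputation is a separate question: leaving it out would pull the estimate towards the null (ratio 0.89–1.00 in the simulations).

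**What to change.** 1. **Handling missing data ({20c}).** Add recorded session completion, from attendance lists and WebApp logs, as an auxiliary predictor when imputing AFQ-Y. It exists only in the active arms, so it needs an arm-specific term. State that it removes only part of the bias if few non-adherers are observed.
2. **Additional analyses ({20b}).** Keep available-case as descriptive and add a sensitivity analysis that departs from missing at random. One option is to add a shift to imputed active-arm scores, from 0 up to the assumed effect (0.50 SD = 6.5 points for self-help, 0.80 SD = 10.4 points for group; higher AFQ-Y is worse). Another is to impute missing active-arm T3 scores from the TAU distribution given baseline. Either or both will do. Report the point at which the conclusion changes.

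The cost is wording in the analysis plan and a few extra model runs on data already collected, with no new participants. Intervals may be slightly wider, and the sensitivity estimate may be less favourable than the primary one. If the analysis plan is already final, the analysis can still be added and labelled as an addition.
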